**Trial registration:**

ClinicalTrials.gov, NCT04028310. Registered on July 18, 2019.

**Supplementary Information:**

The online version contains supplementary material available at 10.1186/s12887-022-03701-8.

## Administrative information

A SPIRIT-Checklist with the page numbers corresponding to each item is available in the Additional file 1.

## Background {6a}

Developmental dyslexia is defined as a severe and persistent impairment that affects the capacity to learn to read despite normal intelligence and in the absence of neurological or psychiatric pathology, visual and auditory sensory deficits, or severe socio-educational deficiencies [1]. This neurodevelopmental disorder is characterized by various underlying neurocognitive deficits [2] and results in an underactivation of the reading network hosted in left occipito-temporo-parietal brain areas, most likely due to abnormalities in connectivity between these areas and more frontal and/or parietal language areas [3, 4]. Dyslexic readers encounter great difficulties in learning and automatizing the decoding of printed words [5], which consists in linking the basic units of written language (letters or graphemes) to the basic units of spoken language (sounds or phonemes). Reading fluency often remains difficult for children with dyslexia and requires a higher cognitive effort in comparison to normally developing children [6, 7]. The prevalence of developmental dyslexia is between 5 and 17% depending on cut-off criteria and language [6]. Dyslexia has severe repercussions on all aspects of school learning, self-esteem and professional development, which makes it a major public health issue [8]. Problems with reading, spelling and associated cognitive functions persist into adulthood [9].

For more than a century, many explanatory theories have been put forward for this complex learning disability without a true consensus ever being reached [10]. Currently, the scientific literature increasingly emphasizes the multifactorial nature of developmental dyslexia at the neurobiological [11, 12], cognitive [13–16], behavioral [17, 18] and environmental level [19]. Family studies indicate an uncertain etiology involving a complex interaction between biological, cognitive, behavioral and environmental factors [20]. That is, biological factors influence cognitive factors, which in turn influence behavior, each one being influenced by an individual’s environment [21]. Moreover, reading involves underlying multimodal cognitive processes that require the interplay of linguistic, visual, phonological, attentional and executive processes.

Developmental dyslexia is defined in current classifications, such as *The International Classification of Diseases (ICD-11) and The Diagnostic and Statistical Manual of Mental Disorders (DSM-5)*, mainly as a specific cognitive impairment of written language [1, 22]. These definitions, which focus on reading and spelling disorders, do not take into account underlying cognitive deficits (UCD) when making a diagnosis. Furthermore, the pathological behavioral manifestations in reading and the UCD may be different for each dyslexic reader. Thus, this complex multifactorial interaction leads not only to a nosographic and etiological multimodality but also to a symptomatologic and diagnostic multimodality. Developmental dyslexia is thus conceptualized as a “multifunctional deficit” [11, 23] or “multifaceted, heterogeneous disorder” [2], in accordance with a multifactorial causal hypothesis [24, 25], involving several UCD, themselves underpinned by the dysfunction of a large circuit of interconnected neural networks [26].

Three main theoretical hypotheses currently guide research on therapeutic interventions of developmental dyslexia: The phonological hypothesis, the visual-attentional hypothesis, and the cross-modal hypothesis. According to the phonological hypothesis, a specific alteration of phonological representations or poor access to phonological representations alters the automatization of grapheme-phoneme associations [14, 27]. This phonological processing deficit is believed to alter the ability to identify, store, retrieve and manipulate phonemes, which are necessary for efficient decoding [16]. Three types of tasks assess phonological representations: Phonemic awareness tasks, such as phonemic segmentation, phonological short-term memory tasks, such as non-word repetition [28], and rapid serial naming tasks such as rapid automatized naming [29, 30]. However, rapid automatized naming (RAN) may be considered as “a microcosm of reading” because like reading task it requires fast multimodal integration and several neurological and cognitive processes: Saccadic eye movements, perceptual recognition, visual attention shifts, working memory, lexical access, and articulatory planning [29]. Furthermore, the relationship between reading and RAN does not remain constant throughout development [31]. Numerous studies and meta-analyses have investigated the effects of phonemic awareness training on reading skills. All of these studies agree that phonemic awareness interventions alone are less effective than phonics instruction that combines phonemic awareness and reading fluency trainings [32–34]. However, all of these interventions have only a moderate short-term effect and a small long-term effect on reading [35]. The effectiveness of phonological short-term memory training on reading skills in dyslexic individuals has not been demonstrated in alphabetic languages but has been demonstrated in a logographic language, Chinese [36]. Finally, the results about the training of RAN have yielded mixed results [37]. For example, De Jong and Vrielink [38] did not find effects, Marinus and colleagues [39] did find some effects but these effects did not generalize to reading. Two very recent studies have shown moderate to strong effects of a rapid automatized naming (RAN) training on reading [40, 41]. In addition, some researchers suggest that this deficit in phonological processing is the consequence of a more fundamental deficit in the perceptual and/or attentional processing of auditory information [42–49]. For example, allophonic perception of speech sounds in subphonemic units can lead to poor discrimination of acoustic differences, a perceptual deficit in phoneme categorization and consequently a deficit in phonological processing. Coherently with this view, one study recently showed the positive effect of phoneme categorization training on reading skills and phonemic awareness [50].

According to the visual-attentional hypothesis, a deficit in the visual processing of grapheme representations also alters the automatization of grapheme-phoneme associations. According to this account, the ability to identify, store and retrieve graphemes is disrupted by a deficit in the perceptual and/or attentional processing of visual information. Three types of deficits have been put forward in support of the visual-attentional hypothesis of dyslexia: Perceptual visual deficits [51], deficits in the temporal and spatial displacement of visual-attention [52–55] and elementary visual-attentional deficits [56]. Perceptual visual deficits are related to a hypothetical impairment of the magnocellular visual system, which preferentially processes information with a low spatial frequency and high temporal frequency. Within this theoretical framework, a visual training program called Direction Discrimination Training (DDT) seems to increase reading and phonological processing skills [57]. Regarding visual and spatial attention deficits, the VHSS (Visual Hemisphere Specific Stimulation) program [58], whose goal is to reinforce the inhibitory capacities of the visual-spatial attention processes, seems to be more effective in improving speed and precision reading skills, compared to phonological awareness training [59]. This deficit in the spatial displacement of attention, i.e. of the attentional focus, has also inspired certain remedial activities such as the intensive use of action video games, which has been observed to have a positive effect on reading speed, phonological short-term memory, attentional abilities and crowding in Italian- and also in English-speaking dyslexic readers [60–62]. The results of a systematic review [24] show that visual-attentional interventions based on visual perceptual training and action video games significantly improve reading without explicit phonological or spelling instruction. The third type of visual-attentional deficit concerns the processing of elementary visual-attentional processes. For example, a reduction in the visual-attentional span, that is the number of letters processed simultaneously during eye fixation, appears to disturb the identification of letters and could explain a disorder in the identification of written words [63]. The Maeva© training program has been shown to increase the visual-attentional span, but also improves phonemic awareness and reading of irregular words [50]. Also within the conceptual framework of an elementary visual-attentional deficit, an imbalance between global and local modes of analysis of a complex visual scene can also alter letter encoding, visual identification of irregular words and stabilization of orthographic representation [64, 65]. The Switchipido© program [66] aims at focusing visual attention on global or local levels of analysis to improve reading skills [64, 67].

A third hypothesis considers a potential deficit in cross-modal integration of letters and sounds as a possible cause of the deficit in the automatization of word decoding and consequently of reading fluency. In this theoretical framework, letter-sound association is possible but the simultaneous letter-sound integration as a single automatized audio-visual object is slowed down [3, 68]. This specific deficiency in the link between the processing of orthographic representations and the processing of phonological representations has been found in child and adult dyslexic readers [69, 70] but also in young children at risk of developing dyslexia [68]. The automatic multisensory integration of a single audio-visual object, “the graphoneme” [71] initially appears to activate the left posterior temporal cortical network and then the entire left occipito-temporal-parietal interactive network involved in reading [3, 72, 73]. GraphoGame© [74], a computer-based reading training program, was developed to foster orthography-phonology associations at multiple grain sizes and automatize orthography-phonology integration through the simultaneous and repeated audio-visual presentation of letters, syllables, words, and sentences in a highly playful interface. Developed in Finland the program has been adapted for French [75] and other languages [76–80]. A meta-analysis found positive effects of intervention using *GraphoGame* (GG) if the program was accompanied by a tutor [81]. The French version of GG is broader and more sophisticated than the research versions included in the meta-analysis. A recent validation study of the French version of GG showed effect sizes of around 0.28 for independent practice with the program [82]. Other intervention programs using non-linguistic audio-visual stimuli also show effects on reading skills [83], but the reasons for the deficit in the audio-visual integration of low-level stimuli are still debated [84, 85].

To summarize, independent of the theoretical underpinnings, all intervention programs have attempted to reduce the reading deficit:Through interventions on the grapho-phonological and/or orthographic reading processes, by proposing successive training sessions to automatize phonological decoding and lexical recoding [86–88] or by intervening specifically either on the grapho-phonological process or on the orthographic process [89–94];Through more specific interventions at the level of an UCD either audio-phonological [95–97], visual [50, 57, 59–61, 98, 99] or audio-visual [83, 100–102];Through combined interventions on reading processes and UCD through programs using “phonics instruction” that combine training of phonological cognitive processes and grapho-phonological conversion procedures [103, 104] or through programs that combine training of visual cognitive processes and spelling and reading procedures [59, 105–107].

Previous work has mainly focused on the validation of remediation methods based on three theoretical domains that may explain developmental dyslexia: Phonological theory, visual-attentional theory, and cross-modal theory. Each causal theory generates different hypotheses and multimodal UCD. However, the expression of these UCD is also highly variable depending on the dyslexic reader [108]. Some dyslexic children show the predicted deficit and others do not. Similarly, intervention programs seem to help some readers but not others. Developmental dyslexia may therefore be the consequence of several UCDs [16] that need to be identified in a first step and treated in a second step in order to construct and automatize optimal grapheme-phoneme associations in a third step [5]. Furthermore, it appears that remediation programs that combine an intervention on both UCD and reading processes may be more effective than programs that intervene only at the level of UCD [33, 34].

The originality of our study protocol is to combine three types of intervention programs that target phonological, visual-attentional and cross-modal UCD using a multimodal remediation approach in a longitudinal study. All participants benefit from the three types of training: Phonological, visual-attentional and cross-modal. For each participant, an initial assessment of the underlying cognitive processes determines a cognitive profile. Similarly, an assessment of reading and spelling skills will determine a reading profile. The cognitive profile and the reading profile of each dyslexic reader defines the specific type of intervention in each domain (e.g., a child can receive 4 different phonological interventions as a function of the profile, see Fig. 1). Thus, each intervention program focuses on both an underlying cognitive process (visual-attentional, phonological or cross-modal) and a reading process (decoding and orthographic processing). Interventions are therefore individualized, systematic, intensive and evidence-based in accordance with DSM-5 guidelines. Furthermore, daily exercises are performed at home on computerized devices in accordance with the general principles of cognitive rehabilitation [109] and the principles of efficiency and generalization of an intervention [88]. Computerized training programs are adapted to each child’s abilities, progression and cognitive functioning. Computerized programs allow home training, ensure reproducible multimodal presentation and increase autonomy, motivation and attention [110]. Each computer-based training program targets a phonological, visual-attentional or cross-modal cognitive process and is systematically associated with reading and writing exercises of words or pseudowords to promote multisensory learning [111, 112]. Carried out in a therapeutic context, this longitudinal prospective study allows for an immediate clinical application.

**Fig. 1 Fig1:**
[figure not shown]
Schematic description of the three intervention programs and the individually tailored training programs

## Objectives {7}

### Main objective

The main objective of this study is to assess whether the combination of three types of intensive interventions (phase 2) improve reading and spelling skills compared to baseline (i.e., non-intensive intervention, phase 1).

### Secondary objectives

Assess the efficiency of each intervention against baseline.Assess the efficiency of each intervention as a function of the severity of the “underlying cognitive deficits”.Assess the effects of intensive intervention (phase 2) compared to baseline (phase 1) on reading interest, academic performance, and self-esteem.Assess the stability of the intervention effects in all of the above measures 2 months after training.

## Trial design {8}

The trial is a two-arm crossover multicenter randomized controlled trial conducted in France with 76 speech-language therapists as associate investigators. Randomization will be ensured by means of block randomization with a 1/1 allocation. The framework of this trial corresponds to its overall objective which is to test the superiority of a multimodal and intensive training compared with a non-specific and non-intensive training. Indeed, all children who come to seek dyslexia therapy with a speech and language therapist deserve to be helped and it is ethically difficult to justify that we postpone a potentially effective intervention for 16 months (i.e., children would lose more than an entire year, which is a lot during such a critical developmental phase). For these ethical reasons, we have decided to not to include a no-training control group.

The experiment will take place in three phases over 16 months (see Fig. 2):Phase 1 (baseline): All dyslexic readers participate in one 30-minute session per week with the speech-language therapist for 8 weeks without intensive home training. Reading and spelling exercises are performed as part of the speech and language therapy.Phase 2 (intervention): All dyslexics receive three types of intensive interventions, phonological (PHO), visual-attentional (VA), and cross-modal (CM), that last 2 month each. The order of the first two interventions (PHO and VA) is swapped in two randomly assigned groups of 60 dyslexics each. All children also participate in one 30-minute session per week with the speech-language therapist. For 15 minutes, the speech-language therapist checks that the at-home training instructions are clearly understood. The rest of the session is focused on reading and spelling exercises.

**Fig. 2 Fig2:**
[figure not shown]
Schematic description of the trial design (see text for details)

CM training takes place at the end of the protocol for two reasons. The first reason is that it might be necessary to first focus on the phonological and visual-attentional processes per se. PHO and VA training should initially improve orthographic and phonological processes and cross-modal training should subsequently re-establish the link between the processing of orthographic representations and the processing of phonological representations. The second reason is that the full randomization of the order of the three types of training would require a much larger sample and more groups. This would increase the risk of not reaching the needed number of inclusions. The number of participants in each group would then be insufficient to obtain sufficient statistical power.

Each training phase lasts for 8 weeks, 15 minutes per day and 5 days per week. Each child benefits from a program adapted to the specific phonological and visual-attentional deficits identified by the cognitive and language profile assessment. For example, children with phonological deficits may receive training to improve phonological awareness and/or phonological short-term memory and/or rapid automatized naming and/or categorical perception (see more explanations p.18). Children with visual-attentional deficits may receive training to improve global-local analysis and/or visual-attentional span. Training will focus on the most impaired deficits. The CM training is the same for all children.Phase 3: All children have one 30-minute session per week with the speech-language therapist over a period of 8 weeks without intensive home training as in Phase 1.

### Main hypothesis

Intensive and specific multimodal training significantly improves reading (fluency, comprehension) and spelling skills compared to a conventional non-intensive and non-specific therapy. These effects of intervention will be tracked after the three training phases (test 5) and 2 months later (test 6).

### Secondary hypotheses

*Hypothesis 1*: Intensive phonological or visual-attentional training is more effective than conventional non-intensive and non-specific therapy*Hypothesis 2*: Intensive, specific, multimodal training (test 5) significantly improves reading interest, academic performance, and self-esteem compared to conventional non-intensive therapy (test 2).*Hypothesis 4*: These intervention benefits should last 2 months later (test 6).*Hypothesis 5*: No significant difference as for the effects on reading skills is expected between phonological versus visual-attentional training (test 3).

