### Statistical analysis

To assess the gains for each dependent variable (reading, spelling and reading comprehension scores) in each group (1 and 2) and for the total sample, we will calculate the means difference and confidence intervals between T1 and T2 (Phase 1 without training), between T2 and T4 (Phase 2 after 16 weeks of training), between T4 and T5 (Phase 2 after 24 weeks of training), and between T5 and T6 (Phase 3 after 8 weeks without training).The gains between T1 and T2 will be compared with the gains between T2 and T4, between T4 and T5, and between T5 and T6 to determine whether the T2T4, T4T5, and T5T6 differences represent a significantly greater gain compared to the no training phase (T1T2).

To measure the effect of each type of training, we will calculate the effect size, *Cohen’s d* or *η*^*2*^, from the gains of each dependent variable. Cohen’s d scores of 0.3, 0.5 and 0.8 are considered to represent small, medium and large effect sizes, respectively.3.To determine whether the order of PHO/VA versus VA/PHO training leads to different effects, we will perform a repeated Anova with cross-over between groups to compare the gains between T2 and T4 of each group, controlling for gains between T2 and T1 without training. This analysis will also allow us to determine if there is a significant difference between the effects of 8 weeks of phonological training and 8 weeks of visual-attentional training between T2 and T3.4.Exploratory factor analysis will verify that all the items in the questionnaires (pre-test and post-test Likert scale) or, failing that, some of them can be combined into a score. If necessary, the composite scores will be analyzed as continuous variables. If not, graphical representations in the form of histograms will be used to visualize the variations, and χ^**2**^ tests will be carried out.

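### Two secondary hypotheses are not tested as stated: no planned contrast sets phonological or visual-attentional training alone against baseline, and a no-difference hypothesis is examined only by a difference test

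*Protocol article*

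**What the plan says.** All references are to the protocol article.

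- **Aim against baseline.** The first item under Secondary objectives is "Assess the efficiency of each intervention against baseline". Hypothesis 1 under Secondary hypotheses is "Intensive phonological or visual-attentional training is more effective than conventional non-intensive and non-specific therapy".
- **Aim between trainings.** Hypothesis 5 is "No significant difference as for the effects on reading skills is expected between phonological versus visual-attentional training (test 3").
- **Contrasts with the baseline phase.** Under Statistical analysis: "The gains between T1 and T2 will be compared with the gains between T2 and T4, between T4 and T5, and between T5 and T6". The first training-phase gain is described as "between T2 and T4 (Phase 2 after 16 weeks of training").
- **Comparison between groups.** The order question is handled by a repeated ANOVA that will "compare the gains between T2 and T4 of each group, controlling for gains between T2 and T1 without training". On PHO versus VA the section adds: "This analysis will also allow us to determine if there is a significant difference between the effects of 8 weeks of phonological training", set against the same length of VA training, from T2 to T3. The general threshold under Statistical methods is 5%.
- **Per-training effect.** "To measure the effect of each type of training, we will calculate the effect size", as Cohen's d or η², from the gains.
- **Data.** Under Secondary evaluation criteria, the five reading tests are given at Test 3 and Test 4 in both groups (G1: PHO, VA, CM; G2: VA, PHO, CM, where CM is cross-modal training).

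**The concern.** The Statistical analysis section lists its contrasts explicitly, and the list does not match the questions asked.

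For Hypothesis 1, the only interval in which a child has had one training and not the other is T2-T3, and T2-T3 is not among the gains compared with T1-T2. A positive T2-T4 result could come from PHO, from VA, from their sum, or from the longer interval. None of these answers whether PHO alone or VA alone beats usual therapy.

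For Hypothesis 5, the prediction is itself a non-significant result, and no margin or interval criterion is given. Under that wording, a smaller or noisier trial is more likely to confirm the hypothesis. At stake is a published statement that the two trainings work equally well, resting on an interval that may include differences as large as the effects the trial hopes to find.

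**Working it through.** **1. Baseline contrasts, laid side by side**

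| Interval | Length | Group 1 | Group 2 | Compared with T1-T2? |
|---|---|---|---|---|
| T1-T2 | 8 weeks | usual therapy | usual therapy | reference |
| T2-T3 | 8 weeks | PHO | VA | no |
| T2-T4 | 16 weeks | PHO then VA | VA then PHO | yes |
| T4-T5 | 8 weeks | CM | CM | yes |
| T5-T6 | 8 weeks | usual therapy | usual therapy | yes |

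T2-T4 pools both trainings in both groups. Its length also matters: if a child gains g per 8 weeks under usual therapy, then T1-T2 = g and T2-T4 = 2g with no training effect at all. No rescaling is stated. T2-T3 versus T1-T2 is 8 weeks against 8. CM does have its own contrast (T4-T5), but only as training given after PHO and VA.

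**2. The plan's sample size**

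Inputs from Sample size: d = 0.700, 55 per group, 10% drop-out, 120 in total. Power and sidedness are not stated. A two-sided 5% two-sample t-test with d = 0.70 and 95% power needs 54.02, rounded up to 55 per group, so the figure reproduces. With drop-out, 110/0.90 = 122.2, close to the stated 120. The d of 0.700 is for intensive therapy against baseline; nothing was sized for PHO versus VA.

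**3. Precision for Hypothesis 5 (unadjusted, in SD of the T2-T3 gain)**

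- SE = √(2/55) = 0.191.
- 95% half-width = 1.982 × 0.191 = 0.378 (0.362 with 60 per group).
- Probability of a non-significant two-sided test (noncentral t, 55 per group): 82% for a true difference of 0.2, 61% for 0.322, 26% for 0.5. With 60 per group the figure for 0.322 is 58%.

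The 0.322 is the literature effect for phonological interventions quoted under Sample size, used here only as a yardstick.

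**4. What an equivalence test could show**

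Power at a true difference of 0 is 2Φ(margin/SE − 1.659) − 1. With 55 per group and margins in SD of the gain, it is 0% for 0.3, about 2% for 0.322, 34% for 0.4, 66% for 0.5 and 86% for 0.6. The margins are assumptions; the article gives none.

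**5. How far this depends on the scale**

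The article takes Cohen's d from the gains but does not say on which SD the 0.322 was computed. If it is in SD of the score, and the correlation between occasions is ρ (assumed, equal variances), the gain has SD √(2(1−ρ)) and the difference becomes 0.322/√(2(1−ρ)) gain SDs:

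| ρ | Gain SD | Difference in gain SDs | Non-significant |
|---|---|---|---|
| 0.5 | 1.000 | 0.322 | 61% |
| 0.8 | 0.632 | 0.509 | 25% |
| 0.9 | 0.447 | 0.720 | 4% |

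The 61% therefore belongs to the gain scale.

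**6. The model for T3 and T4**

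Assumptions: 54 per group (120 less 10%), ρ = 0.8, equal correlations, score-SD scale, SE = √(2v/54), half-width 1.96 × SE. The last column is the chance of a non-significant result at a true difference of 0.322.

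| Analysis | v | SE | Half-width | Non-significant |
|---|---|---|---|---|
| Difference of gains (group × phase) | 6(1−ρ) = 1.20 | 0.211 | ±0.41 | 67% |
| Gain alone | 2(1−ρ) = 0.40 | 0.122 | ±0.24 | 25% |
| Gain, T1-T2 gain as covariate | 1.5(1−ρ) = 0.30 | 0.105 | ±0.21 | 14% |
| ANCOVA on T1 and T2 scores | 1−2ρ²/(1+ρ) = 0.289 | 0.103 | ±0.20 | 12% |

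Only the first row is poor. The covariate version and ANCOVA barely differ.

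**The case against.** **Hypothesis 5.** It states an expectation, and nowhere does the article say that a non-significant result will be reported as equivalence. A reader might infer that it does; the text does not go so far. What stands is that the hypothesis is worded so that non-significance agrees with it and that no other criterion is offered.

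**Effect of each training.** A reader might infer that the effect of PHO or VA is never estimated. That is too strong. An effect size per type of training is planned and Test 3 is given to both groups. What is missing is a named comparison of T2-T3 with T1-T2.

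**Randomised status.** It is tempting to call both hypotheses the trial's randomised questions. Only PHO versus VA at T3 and order at T4 are randomised. Hypothesis 1 is a before-after comparison within children, since all pass through phase 1 first.

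**The ANOVA.** Reading it as group × phase triples the variance of the gain and gives the 67% figure. But controlling for a gain ordinarily means using it as a covariate, and then the loss against ANCOVA is negligible. Moreover, a group × phase model containing the T1-T2 and T2-T3 gains would yield the Hypothesis 1 contrast as a simple effect. One cannot hold both that the contrast is absent and that the variance is tripled. The text is ambiguous, so this remains a request for clarity.

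**Documents not shown.** A fuller protocol or analysis plan may settle some of this. The article nevertheless lists its contrasts explicitly, and that list does not match its own objectives.

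**Conclusion.** The point holds in two parts, with a minor third.

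1. No listed contrast isolates PHO or VA against the baseline phase, as Hypothesis 1 and the first secondary objective require. This follows from the text and needs no assumption.
2. Hypothesis 5 is examined only by a 5% difference test, so imprecision works in its favour. On the gain scale, unadjusted, with 55 per group, the 95% interval is about ±0.38 SD, and a true difference of 0.322 SD would be missed about 61% of the time. These figures assume a two-sided test. They improve if 0.322 is a score-SD effect and occasions are highly correlated, but the fault in the logic remains whatever the precision.
3. The repeated ANOVA should be specified. Whether this matters in practice depends on a reading the article leaves open.

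The correlation between occasions and every margin used here are assumptions. The matter should be corrected before analysis. It concerns secondary questions and does not touch the main comparison of phase 2 with phase 1.

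**What to change.** - **Hypothesis 1.** Add T2-T3 versus T1-T2 within each group: PHO in group 1, VA in group 2. Report it as a within-child, non-randomised comparison. With 55 children per group, a paired test has about 65% power for 0.322 and 95% for 0.5, in SD of the within-child difference of gains. Label T4-T5 as cross-modal training after PHO and VA.
- **Hypothesis 5.** Choose one of two routes. Either fix and justify an equivalence margin before analysis and require the 90% interval for PHO minus VA at T3 to lie inside it, or restate the hypothesis as an estimate with its interval and make no claim of no difference. A margin of 0.322 SD would equal the whole cited phonological effect, so a training with almost no effect could pass; a margin that wide would need a strong argument. If no justifiable margin gives useful power, take the second route.
- **Model (minor).** State that PHO versus VA at T3 and order at T4 are estimated by ANCOVA with the T1 and T2 scores as covariates, and not as a difference of gains.

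The cost is a few sentences, two contrasts and possibly one margin. No new visits, tests or children are needed.
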